### 2.4. Dietary Intervention with QDP and CDC

Both dietetic approaches (QDP and CDC) are based on the same dietary recommendations in HT. To identify studies reporting dietary recommendations in HT or hypothyroidism (reviews) and investigations on diet and health outcomes in HT or hypothyroidism (original papers), the PubMed, Embase, and Cochrane Library databases (to March 2019) and the bibliographies of key articles were searched. Based on the data extracted, dietary recommendations for HT were established. Justification for these recommendations is presented in detail in the discussion (Section 3.1 and Section 3.2). 

General dietary guidelines for HT subjects will be distributed as a printed leaflet, which was the same for all participants in both the QDP and CDC groups (Table S1, in Polish: Table S2). In the leaflet, there are universal dietary guidelines which, if adhered to, may reduce the risk of health disorders. Similar pro-healthy dietary guidelines are widely promoted for the general population [27,28,29]. 

In the CDC group, dietetic counseling will be conducted in a conventional manner. Respondents will receive detailed oral explanations and printed sample menus given by a dietician. In this model of subject–dietician cooperation, the dietician is more involved while the subject is less (being more passive).

In the QDP group, dietetic counseling will be supported with a simple tool containing two lists: (A) foods recommended for consumption (seven items) and (B) foods with limited consumption (six items), both with an indicated consumption frequency per day/week/month (Table 3 and Table 4, in Polish: Tables S3–S4). To develop both lists, we summarized data collected from the literature search and extracted recommended frequencies of food consumption, dividing foods on those recommended for more frequent consumption (list A) or less frequent consumption (list B). If the state of knowledge was unclear or findings were contradictory or poorly documented, then guidelines for the general population were adopted [30] to establish consumption frequency per day/week/month. Each food list is developed as a graphic–text self-monitoring diary to help patients in food selection and to exercise self-monitoring of food consumption and facilitate compliance with dietary guidelines. The printed version of the self-monitoring diary will be distributed, and participants will be asked to complete a diary for six months and return it during a visit. Respondents’ adherence to dietary guidelines will be expressed in points; one point per each compliance to each recommendation will be assigned. All points will be summarized to express an adherence score to the QDP an Adherence Score to the QDP (AdhS; ranged 0-13 points). Data from six months will be collected, and the mean AdhS will be calculated. The AdhS will be considered on three levels—low (0–4 points), average (5–9 points), and high (10–13 points)—and interpreted; more points indicates better compliance with dietary guidelines.

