### 1.1. Research Objective and Hypothesis

The current state of knowledge related to diet in HT is far from satisfactory, while many HT subjects experience many disorders and report reduced quality of life [13,14,18,23]. There is a strong need to summarize the evidence and develop dietary recommendations that are simple for HT subjects to understand and implement daily over a long-term period, and are useful for dieticians and other health professionals. The conventional approach to dietetic counseling is a structured process aimed at supporting individual patients to modify their dietary behaviors to improve health outcomes [24]. Conventional dietetic counseling is based on the development of individual recommendations and formulating detailed guidelines, which may prove difficult for patients to follow over the long term due to growing fatigue, lowering of motivation, the time required, and difficulties maintaining subject compliance to the diet [25]. Mitchell et al. [24] reported that dietetic counseling appears to be effective, e.g., in improving diet quality, diabetes outcomes, and weight loss outcomes, while limited evidence was found for the effectiveness of direct dietetic counseling alone in achieving outcomes relating to plasma lipid levels and blood pressure. The authors suggested that future research might explore novel nutrition counseling approaches.

There are three aims of the study: (1) to develop a qualitative dietary protocol (QDP; ‘Diet4Hashi’) as a simple, graphic–text tool dedicated TH subjects, (2) to evaluate the use of the QDP in dietetic counseling compared to conventional dietetic counseling (CDC) in HT women, (3) to assess the impact of both the QDP and the CDC on diet quality, quality of life, adiposity, and metabolic parameters. It is planned to develop a food-only protocol without considering the use of supplements because an adequate, well-balanced diet should be the first step in a dietary approach to improving health.

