The research hypotheses are:Dietetic counseling with the use of a qualitative dietary protocol can facilitate patient understanding and long-term adherence to dietary recommendations compared to conventional dietetic counseling.A well-composed diet supported with a simple, qualitative dietary protocol, by improving food selection and diet quality, can improve the quality of life of HT subjects, reduce adiposity, and improve metabolic parameters. Furthermore, a better effect of a qualitative dietary protocol than conventional dietetic counseling is possible.

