### 1.2. Study Design

The study is designed as a single-center dietary intervention lasting six months, with a random allocation of HT women into two parallel groups: experimental and control. In the experimental group, the QDP will be applied, while the CDC will be applied in the control group. The QDP is based on subject self-monitoring supported with a graphic–text tool to help them in food selection and adequate food frequency consumption, while the CDC will be supported by an oral explanation and printed sample menus given by dietician. Both approaches include the same dietary recommendations for HT, extracted from the literature, but differ in subject–dietician cooperation. 

The schedule of the enrolment, intervention, and data collection is presented in Table 1. All data will be collected at the same time for both groups, with one exception. The experimental group, supported with a graphic–text tool, will be asked to complete self-monitoring diaries during the six months of the study.

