### 2.12. Statistical Analysis

Categorical variables will be presented as a sample percentage (%) and continuous variables will be presented as means with a 95% confidence interval (95%CI) or medians with an interquartile range (IQR) for variables with normal or non-normal distribution, respectively. To assess the impact of dietetic counseling and verify the differences between the experimental and the control group, two-tailed tests will be applied; *p*-values < 0.05 will be considered significant. 

The normality of variable distribution will be verified with a Kolmogorov–Smirnov test before the statistical analysis. For continuous variables, e.g., diet quality scores, AdhS, scores of QoL, nutrition knowledge score, TFTs, markers of adiposity, metabolic parameters, and changes after a six-month follow-up with respect to baseline will be verified with a T-test for dependent samples or a Mann–Whitney test, for variables with normal or non-normal distribution, respectively. For categorical variables, logistic regression modeling will be applied to determine the chance of the occurrence of high diet quality, high AdhS, high QoL, as well as low adiposity and elevated metabolic parameters. The odds ratios (ORs) and 95% confidence intervals (CIs) will be calculated. The significance of ORs will be verified with Wald’s statistics. A crude model and models with an adjustment for confounders will be created. All analyses will be performed with Statistica software (version 13.3 PL; StatSoft Inc., Tulsa, OK, USA; StatSoft, Krakow, Poland).

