## Figures and Tables

**Figure 1 ijerph-16-04841-f001:**
[figure not shown]
Sample collection chart.

**Table 1 ijerph-16-04841-t001:** Timetable of data collection.

Timing	Activities	Group	
		Experimental	Control
T0 visit (enrolment)	Eligibility screening; Written informed consent; Assignment to the experimental or control group.	✕	
T1 visit (baseline)	Data collection of diet quality and other lifestyle factors, quality of life, nutrition knowledge, sociodemographic factors.	✕	✕
	Measurements of adiposity, metabolic parameters, and thyroid function.	✕	✕
	Dietetic counseling.	QDP	CDC
Between visits	Home collection of dietary data with self-monitoring.	✕	
T2 visit (1-month follow-up)	Dietetic consultation to boost compliance with dietary guidelines.	✕	✕
	Data collection of diet quality and other lifestyle factors, quality of life.	✕	✕
	Measurements of adiposity and metabolic parameters.	✕	✕
Between visits	Home collection of dietary data with self monitoring.	✕	
T3 visit (6-month follow-up)	Data collection of diet quality and other lifestyle factors, quality of life, nutrition knowledge.	✕	✕
	Measurements of adiposity, metabolic parameters, and thyroid function.	✕	✕

QDP—a qualitative dietary protocol; CDC—conventional dietetic counseling.

**Table 2 ijerph-16-04841-t002:** Participant eligibility criteria. BMI: body mass index.

**Inclusion Criteria**: women age >18 and <60 years; prior diagnosed Hashimoto thyroiditis: hypothyroidism or subclinical hypothyroidism; medical certificate for levothyroxine treatment or other thyroid hormones; agreement to take part in the study;

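### One six-month mean AdhS cannot show whether adherence lasted in the QDP arm, and its bands leave some means without a level

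*Protocol article*

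**What the plan says.** Section 1.1 of the protocol article argues that conventional counseling "may prove difficult for patients to follow over the long term due to growing fatigue, lowering of motivation". Its first hypothesis is that counseling with the QDP "can facilitate patient understanding and long-term adherence to dietary recommendations compared to conventional dietetic counseling".

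Adherence is measured by diary in one arm only (section 1.2): "The experimental group, supported with a graphic–text tool, will be asked to complete self-monitoring diaries during the six months of the study". Section 2.4 gives one point per recommendation met, for a range of 0–13, and then states: "Data from six months will be collected, and the mean AdhS will be calculated". It sets three levels: low 0–4, average 5–9, high 10–13.

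Section 2.12 states that "changes after a six-month follow-up with respect to baseline will be verified", and lists high AdhS among the outcomes for logistic regression. Table 1 schedules a one-month visit (T2) in both arms. It includes a "Dietetic consultation to boost compliance with dietary guidelines" and repeats diet quality, quality of life, adiposity and metabolic measurements. The next and last visit is T3 at six months.

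**The concern.** The protocol's case for the QDP is that adherence to conventional advice fades. The informative period is therefore the five months between the booster consultation at T2 and the visit at T3, when no consultation is scheduled. A six-month average blends that period with the first weeks, when motivation is likely to be highest. A participant whose adherence is falling can then receive the same label as one who is holding steady.

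Two smaller matters belong with this. The bands are written for whole points but applied to a mean, so a high-versus-not-high outcome is undefined for some participants. And the T2 outcome data, collected in both arms, have no role in the stated analysis. At stake is what the trial can say about persistence. The month-6 comparison and the sample size are unaffected.

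**Working it through.** **Inputs.** Seven list A items and six list B items (section 2.4), so the maximum is 7 + 6 = 13, which agrees with the stated range. The bands cover 5 + 5 + 4 = 14 values, which is every whole number from 0 to 13. They are complete for a single whole-point score. The question is what happens once scores are averaged.

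**Scoring interval (assumed).** Section 2.4 does not say how often the 13 points are assigned. The diary sheets in Tables 3 and 4 run from day 1 to day 31 of a month, and two limits are monthly (soybean and millet; alcohol). A month is therefore the shortest period over which all 13 items can be scored. Six monthly whole-point scores are assumed below.

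**Loss of order.** Mean AdhS = (sum of six monthly scores) / 6. The paths are illustrations.

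| Monthly scores | Mean | Level | Mean of months 5–6 |
|---|---|---|---|
| 10, 10, 10, 10, 10, 10 | 60/6 = 10.0 | high | 10.0 |
| 13, 13, 12, 9, 7, 6 | 60/6 = 10.0 | high | 6.5 |
| 9, 9, 9, 9, 9, 9 | 54/6 = 9.0 | average | 9.0 |
| 13, 12, 10, 8, 6, 5 | 54/6 = 9.0 | average | 5.5 |
| 5, 6, 8, 10, 12, 13 | 54/6 = 9.0 | average | 12.5 |

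The second path falls by 1.6 points a month (least-squares slope), the fourth by 1.71, and the fifth rises by 1.71. As a bound, a high mean needs a total of 60. Four months at 13 give 52, leaving 8 for months 5 and 6, an average of 4.0. A high six-month mean is thus compatible with late adherence in the low band.

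**Unclassified means.** Possible means are k/6 for k = 0 to 78, which is 79 values. Those strictly between 4 and 5 are k = 25 to 29, and those strictly between 9 and 10 are k = 55 to 59, so 5 + 5 = 10 of 79 have no level. The choice of repair matters. Rounding half up would make k = 57, 58 and 59 (9.50, 9.67, 9.83) high, whereas a cut at ≥10 would not.

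**What the other outcomes show.** Month-6 BMI, waist, body fat, blood pressure, glucose and lipids describe the state at that visit, and the overall ThyPRO item covers the preceding four weeks (section 2.7). A response lost by month 6 therefore gives a smaller change from baseline. The diet quality scores differ, because they ask about the last 12 months (section 2.5). Only 6/12 of that window follows baseline at T3, and 1/12 at T2. A steady change of 0.5 for six months and a change of 1.0 for three months followed by none both average 0.25 over the window (6 × 0.5/12 and 3 × 1.0/12). The diet scores cannot stand in for the missing adherence course.

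**The case against.** The strongest reply has four parts.

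- **An article condenses a fuller plan.** Monthly AdhS summaries and the use of T2 may be described elsewhere, and section 2.4 does not say that the mean is the only summary. This has force for T2, where the fair statement is only that no stated comparison uses it. It has less force for AdhS, because the article itself fixes both the mean and the bands.
- **Month 6 already tests durability.** A reader might infer that an early response followed by decline would look the same as a sustained one on every outcome, or that no planned result bears on lasting benefit. The documents do not support either. The adiposity, metabolic and quality-of-life values at T3 are end-state measures, taken five months after the last scheduled consultation. They cannot separate a modest steady effect from a larger early effect that faded to the same level, but they do register a lost response.
- **Better AdhS timing does not test hypothesis 1.** AdhS exists only in the QDP arm, so no summary of it compares adherence with CDC. This stands, and any report of AdhS should say so.
- **Change from T2 to T3 is a poor persistence test.** It starts from a value that treatment has already affected. Suppose quality of life has changed by −8 points at T2 and −10 at T3 under QDP, and by 0 and −5 under CDC (assumed values; lower is better). QDP is ahead by 8 and then by 5 points, yet the T2-to-T3 changes are −2 and −5, which favors CDC. This also stands and shapes the fix.

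It is also true that 10 of 79 counts possible values and not participants, and that the path ending at 6 describes average late adherence, not a participant who has given up.

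**Conclusion.** The point holds for AdhS. A single six-month mean does not measure sustained adherence, and it can give the high level to a QDP participant whose months 5–6 average is 6.5 or, at the extreme, 4.0. The bands leave 10 of 79 possible means undefined for an outcome that section 2.12 intends to model. The figures rest on monthly whole-point scoring. The loss of order does not, since any average over time has it.

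For outcomes measured in both arms the point is narrower: the month-6 contrast is sound as a test of benefit at that time, and what goes unreported is the path to it, for which T2 data will exist. How often real participants would be misclassified cannot be estimated from the documents. The change is worth making, but the main comparison does not depend on it.

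**What to change.** 1. State that AdhS is scored per month and report its course over months 1 to 6. Use the months 5–6 score as the QDP-arm measure of sustained adherence; the six-month mean can stay as a summary.
2. Define the levels as <5, 5 to <10 and ≥10, so that every mean has one.
3. State that AdhS is a within-arm measure and cannot test adherence against CDC.
4. For quality of life, adiposity and metabolic outcomes, report the baseline-adjusted between-arm difference at both T2 and T3, for example from a repeated-measures model with arm-by-visit terms. Keep month 6 as the main contrast, and do not use the T2-to-T3 change alone as the test of persistence. Leave the 12-month-recall diet scores out of this step.

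The cost is revised analysis wording and a few extra secondary estimates, which should be labeled as such. The diaries and visits are already scheduled, and the sample size does not change.

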### 2.5. Diet Quality 

To collect dietary data, the semi-quantitative food frequency method will be applied, and a food frequency questionnaire (KomPAN) will be used. The KomPAN questionnaire consists of 46 food items and includes a comprehensive variety of foods usually consumed in Poland [30]. The KomPAN questionnaire has been assessed in healthy/unhealthy subjects as reliable tools with acceptable to very good reproducibility [30,31]. To assess diet quality, two predefined diet quality scores (the a priori approach) will be used: pro-Healthy-Diet-Index (pHDI) and non-Healthy-Diet-Index (nHDI).

Participants will be asked to indicate the average frequency of consumption of each food item over the 12 last months. Enrolled participants will receive a questionnaire from trained researchers, who will provide guidance and assistance as required on a one-to-one basis. 

To indicate food frequency consumption, respondents will choose one of six categories (converted into daily frequency): ‘never’ (0 times/day), ‘1–3 times a month’ (0.06 times/day), ‘once a week’ (0.14 times/day), ‘few times a week’ (0.5 times/day), ‘once a day’ (1.0 time/day), or ‘few times a day’ (2.0 times/day) [31]. Daily frequencies of 24 food items will be used to calculate pHDI and nHDI. The pHDI includes 10 food items: wholemeal bread/bread rolls, coarse-ground groats, milk, fermented milk drinks, cheese curd products, white meat, fish, legumes, fruit, and vegetables. The nHDI includes 14 food items: white bread and bakery products, white rice and fine-ground groats, fast foods, fried foods, butter, lard, cheese, cured meat/smoked sausages/hot dogs, red meat, sweets, tinned meats, sweetened carbonated or still drinks, energy drinks, and alcoholic beverages. Daily frequencies of the consumption of the selected 10 (pHDI) or 14 (nHDI) food items will be summed up and recalculated into a range of 0%–100% points according to the questionnaire’s manual [30]. A higher percentage of points reflected greater adherence to the diet quality score, i.e., for pHDI – better diet quality and for nHDI – worse diet quality.

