### 2.6. Other Lifestyle Factors 

Self-reported data related to physical activity, time spent in front of a screen, and sleep duration (over the 12 last months), as well as smoking status will also be collected with the KomPAN questionnaire [30,31]. 

Physical activity in leisure time will be determined by choosing one of three categories: low (sitting, watching TV, reading, light housework, walking less than 2 h a week), moderate (walking, cycling, moderate exercise, working at home/garden, or other light physical activity performed 2–3 h/week) or high (cycling, running, gardening, and other sports/recreational activities requiring physical effort over 3 h/week). Physical activity at work will be determined by choosing one of three categories: low (more than 70% of time spent sedentary), moderate (about 50% of time spent sedentary and 50% active), or high (about 70% of time spent active or physical labor of high intensity). Screen time, defined as time spent watching TV or using computer/tablet (including work), will be determined by choosing one of six categories: <2 h, 2 to <4 h, 4 to <6 h, 6 to <8 h, 8 to <10 h, 10 h or more. Sleep duration during weekdays will be determined by choosing one of three categories: ≤6 h/day, >6 to <9 h/day, or ≥9 h/day. The same categories will be chosen for sleep duration during the weekend. Smoking status will be collected for the past and present (yes, no), and dichotomous categories will then be created: (i) non-smoker or past smoker, (ii) current smoker.

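### Diet quality is recalled over 12 months at every visit, so half of the six-month window precedes counselling and the measured change is attenuated to about 50%

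*Protocol article*

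**What the plan says.** Section 2.5 gives a single recall window for KomPAN: "Participants will be asked to indicate the average frequency of consumption of each food item over the 12 last months". Section 2.6 uses the same window for three lifestyle items: "Self-reported data related to physical activity, time spent in front of a screen, and sleep duration (over the 12 last months". Neither section names another window for follow-up.

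Table 1 starts counselling at T1 (baseline) and schedules two later visits, "T2 visit (1-month follow-up" and "T3 visit (6-month follow-up". At T2 both groups have "Data collection of diet quality and other lifestyle factors, quality of life", and at T3 "Data collection of diet quality and other lifestyle factors, quality of life, nutrition knowledge". Section 1.2 gives the length of the intervention: "The study is designed as a single-center dietary intervention lasting six months".

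Diet quality is one of the outcome domains in the third aim (Section 1.1). Section 2.12 tests its change from baseline to six months and models high diet quality by logistic regression.

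**The concern.** The recall window is twice as long as the intervention. A woman who follows the instruction at T3 has to average six months of her old diet with six months of her new one, while her T1 answer is entirely old diet. The difference between the two answers therefore understates what changed. Both arms are counselled and both are attenuated, so the contrast between the qualitative dietary protocol (QDP) and conventional counselling (CDC) shrinks in the same proportion.

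This matters because improved diet quality is the mechanism named in the second hypothesis (Section 1.1). A small or null result on pHDI and nHDI could reflect the wording of the question as easily as the counselling. Nothing else in the plan fills the gap. The real-time diary is kept in the experimental group only, so it cannot support a comparison between arms. The questionnaire limitations in Section 3.3 cover memory, an incomplete food list and social desirability, but not this overlap. Elsewhere the protocol uses a short window: Section 2.7 refers to the last four weeks in the quality-of-life questionnaire.

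**Working it through.** **Inputs**
- Recall window: 12 months (Sections 2.5 and 2.6).
- Time since counselling began: m = 1 month at T2 and m = 6 months at T3 (Table 1).
- Two-sided 5% test (Sections 2.11 and 2.12).
- 50 per arm with 20% drop-out (Section 2.11): 50 × 0.8 = 40 evaluable per arm.
- Effect and SD for pHDI or nHDI: not given, so assumed below. There is no figure in the plan for diet quality to reproduce.

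**Step 1: share of the window before counselling.** Share = (12 − m)/12.
- T3: 6/12 = 50%.
- T2: 11/12 = 92%.

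**Step 2: share of the true change that is reported.** If recall is even over the window and the diet changes fully at baseline, the reported share is m/12.
- T3: 6/12 = 50%.
- T2: 1/12 = 8%.

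Example on the frequency scale of Section 2.5: a food moves from 0.5 to 1.0 times a day at baseline, a true change of 0.5.
- True 12-month average at T3: 0.5 × 6/12 + 1.0 × 6/12 = 0.75, a change of 0.25.
- True 12-month average at T2: 0.5 × 11/12 + 1.0 × 1/12 = 0.54, a change of 0.04.

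Neither average is an answer option on the six-category scale. A single item would be rounded to a category, so the 50% describes an average tendency and not each item.

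**Step 3: sensitivity to the two assumptions.**
- If women weight recent diet more, the loss is smaller. If the last six months carried 75% of the weight, 75% of the change would be reported.
- If the diet changes gradually, the loss is larger. With a linear change over six months, the mean over those months is half the final change, and 0.5 × 6/12 = 25% of it would be reported at T3.

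**Step 4: illustrative power at T3.** With a two-sample t test and 40 per arm, 80% power corresponds to a standardised difference d = 0.634. The normal approximation gives (1.960 + 0.842) × √(2/40) = 0.626.

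Let v be the share of change-score variance that comes from true differences in change. Halving the reported change cuts that part of the variance to a quarter and leaves reporting error as it was. The SD is then multiplied by √(1 − 0.75v), and the effective difference is 0.5 × 0.634/√(1 − 0.75v).

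| v | SD factor | effective d | power at T3 |
|---|---|---|---|
| 0 (SD unchanged) | 1.000 | 0.317 | 29% |
| 0.25 | 0.901 | 0.352 | 34% |
| 0.50 | 0.791 | 0.401 | 42.5% |
| 0.75 | 0.661 | 0.479 | 56% |
| 1 (all true change) | 0.500 | 0.634 | 80% |

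For other assumed true effects, the range from v = 0 to v = 1 is:
- d = 0.5: 20% to 60%.
- d = 0.8: 42% to 94%.
- d = 1.0: 60% to 99%.

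With 75% of the change reported and an unchanged SD, d = 0.75 × 0.634 = 0.476 gives about 56%.

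**The case against.** The strongest reply is that the article states the window once and never says that it is repeated at T2 and T3; visit-specific instructions could sit in a fuller document. That is possible. But the article gives one window for one questionnaire and schedules that questionnaire's data at three visits, so keeping the window is the natural reading. The point is conditional on it.

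A second reply is that women do not average evenly and may report mostly their recent diet. This stands and would reduce the loss. However, the measure then works best when the instruction is not followed, although trained researchers give one-to-one guidance on it. How far recent diet dominates could also differ between the arm that keeps a diary for six months and the arm that does not.

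A third reply is that a 12-month window at both T1 and T3 spans all seasons and keeps the form whose reproducibility is cited. Both are real advantages, and the fix gives them up. Reproducibility, though, does not show that the form can detect change after six months.

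Four stronger readings are tempting, and the documents do not support them:
- *Diet quality cannot show any change.* Under the stated assumptions about half of the change remains visible at T3. This is attenuation, not blindness.
- *A planned T2 test is lost.* Table 1 collects T2 data, but Section 2.12 and the Abstract speak only of baseline and six months. The 92% describes the data collected and not a stated analysis.
- *Power falls to 29%.* That is the low end of the range in the table, for an effect size the protocol does not state.
- *The trial as a whole is underpowered by this.* The sample size rests on overall quality of life and BMI (Section 2.11), and neither uses KomPAN.

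**Conclusion.** The point holds for pHDI and nHDI, and for the 12-month lifestyle items if their change is analysed. Read as written, half of the T3 recall window lies before counselling. The six-month change is then attenuated to about 50%, given even recall and an immediate change of diet. Recency-weighted recall would lessen the loss and gradual change would deepen it. The distortion runs towards zero for the within-group change and for the QDP-versus-CDC difference, and analysis cannot undo it afterwards. The cost in power cannot be fixed from the documents; for an effect that would otherwise have 80%, it lies between a fall to about 29% and no loss. It should be corrected before baseline data are collected, but it does not touch the outcomes on which the trial is sized.

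**What to change.** In Section 2.5, state one short recall window, no longer than the time since baseline (for example the last month), and use it identically at T1, T2 and T3 in both arms. Do the same for the 12-month items in Section 2.6 if their change will be analysed. If a description of habitual diet is wanted, ask the 12-month version once more at T1 only. None of the follow-up window then precedes counselling.

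Make the between-arm difference in change the main diet-quality comparison. Recruitment runs from October to December (Section 2.2), so T3 falls roughly from April to June. A short window would set an autumn or winter diet against a spring or early summer one. Season affects both arms equally but confounds the within-group before-after test in Section 2.12.

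The change itself is a line in the questionnaire instructions. Its real costs are more seasonal variation and a departure from the form whose reproducibility Section 2.5 cites. If the 12-month form is kept, list the overlap among the limitations in Section 3.3 and do not interpret T2 diet quality as an effect of the intervention.
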